3	NIATx Fidelity Scale^3^	NIATx strategy fidelity and extent of and duration to complete activities (SIC)		X		
1	Program characteristics^1^	Program Size (Admissions), Program Type, ASAM Levels of Care, Payment Sources	X	X	X	X
2	Patient Characteristics	Age, Gender, Race, Ethnicity	X	X	X	X

State of Washington staff will be trained on how to conduct DDCAT and CFIR Index assessments by co-PI ([name]). Two-person teams will schedule and conduct each DDCAT assessment. Additional training or consultation will help answer questions identified at the site visits. Program characteristics are collected during the DDCAT assessments

Data will be collected by the state of Washington staff and NIATx coaches using standardized instruments for each program participating in the study

NIATx Fidelity scoring (Total and 7 subscale scores are organized by preparation, implementation and sustainment phases) will be assessed by two person teams at the end of the active implementation period for each program. Data sources will include a composite of interviews, review of walk-through results, change project forms, coach notes and sustainability plans

At the time of the study, Washington State was transitioning to Managed Care Organizations (MCOs) to pay for the delivery of substance use disorder (SUD) and mental health (MH) services. The transition involved integrating data from two systems: 1) the Treatment and Assessment Reports Generation Tool (TARGET), covering SUD clients and services; and 2) the Mental Health Consumer Information System (MH-CIS), covering community MH clients and services into a new Behavioral Health Data System (BHDS). The study will capitalize and leverage the State of Washington’s experience in utilizing standardized state-wide clinical management information databases for addiction and mental health treatment [67–70]. Implementation penetration outcomes will assess changes in the proportion of patients screened, diagnosed and receiving integrated psychosocial or medication services (Aim 2). The services data will be extracted from the BHDS as well as TARGET and MH-CIS legacy systems. It will include de-identified client level data for all patient admissions to study programs within a 45-day window before and after each DDCAT assessment date (Additional file 1). The information will be transferred to the study team using appropriate security protocols.

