Aim 3 will evaluate variation in the extent of, and fidelity to, NIATx strategies. The specific hypothesis is that programs with more facilitating factors, evaluated using the CFIR Index dimensions, will be more likely to complete the NIATx protocol and to do so with greater participation and fidelity. The programs are the unit of analysis, and the primary predictor variable is the number of factors that support implementation. There are two dependent variables, a continuous variable indicating the proportion (%) of the 22 NIATx tasks completed (SIC) and a continuous variable indicating the degree of fidelity to the NIATx protocol (1 to 5-point scale). Multiple regression analyses will be used to evaluate both outcome variables. Characteristics of the sites that are associated with the outcomes will be added as covariates in the regression models in order to evaluate the effect of the CFIR Index dimensions (e.g., Perceptions of the System and Community Score) after controlling for other predictors. Power for the two-tailed multiple regression analysis (α = 0.05) across 50 programs, and 5% of the variance explained by the covariates, is 79% power to detect a change in R^2^ of 15 and 82% power to detect a change in R^2^ of 16%, when adding the primary predictor to the model.

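### Aim 3 lets association with the outcome decide which site covariates enter a regression of about 50 programs; this often omits modest confounders and can, under some conditions, raise the type I error of the CFIR test

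*Protocol article*

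**What the plan says.** The Specific aim 3 text under Data and power analysis plans multiple regressions with the program as the unit. There are two dependent variables: the share of NIATx tasks completed and the NIATx fidelity score. On the predictor it says "the primary predictor variable is the number of factors that support implementation". This is an observed property of the program, not an assigned one.

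On adjustment it says "Characteristics of the sites that are associated with the outcomes will be added as covariates in the regression models", and gives the purpose: "in order to evaluate the effect of the CFIR Index dimensions (e.g., Perceptions of the System and Community Score) after controlling for other predictors". It names no candidate characteristics and does not say how association is judged. A characteristic's relation to the CFIR Index plays no part in the rule.

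The power statement is "Power for the two-tailed multiple regression analysis (α = 0.05) across 50 programs", with "5% of the variance explained by the covariates". It gives "79% power to detect a change in R^2^ of 15" and "82% power to detect a change in R^2^ of 16" (both in percent). The number of covariates is not stated. Trial status reports 49 programs randomised.

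Table 2 (Data collection/variables) lists the program characteristics collected, "Program Size (Admissions), Program Type, ASAM Levels of Care, Payment Sources", without tying them to the Aim 3 model.

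**The concern.** Programs with more facilitating factors may also differ in size, type, funding or level of care, and these may themselves affect how fully and faithfully NIATx is carried out. Because CFIR readiness is not randomised, covariate adjustment is the only protection that hypothesis H3 has against such confounding.

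A rule that admits a characteristic only if it is associated with the outcome is weak protection at this sample size. A confounder with a modest effect will usually fail the screen and stay out, and its effect then loads onto the CFIR coefficient. The usual p-value takes no account of the selection step. Screening each outcome separately can also produce two CFIR coefficients adjusted for different things. At stake is whether support for H3 reflects facilitating factors or residual confounding by measured site characteristics.

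**Working it through.** **1. The plan's power.** Inputs from Specific aim 3: N = 50, two-sided alpha 0.05, covariate R-squared 0.05, one added predictor. The number of covariates k is not given.

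- Formula: f² = ΔR² / (1 − 0.05 − ΔR²), u = 1, v = 50 − k − 2, λ = f²(u + v + 1), non-central F.
- With k = 7, v = 41 and u + v + 1 = 43.
- ΔR² = 0.15: f² = 0.15/0.80 = 0.1875, λ = 8.06, power 79.2%.
- ΔR² = 0.16: f² = 0.16/0.79 = 0.2025, λ = 8.71, power 82.2%.

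The stated 79% and 82% are therefore reproduced, but k = 7 is inferred by fitting, and k = 6 to 9 stays within 2 points. Under the other convention, λ = f²N, the results are about 85% and 87%. More covariates cost power: k = 10 gives 76% and 79%, k = 12 gives 74% and 77%, and k = 12 with 49 programs gives 73% and 76%.

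**2. How often a confounder is missed.** Assumed screen: marginal association with the outcome at p < .05. If m equal, independent confounders share the plan's 5%, each correlates r = √(0.05/m) with the outcome.

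Hand check for m = 1: r = 0.2236 and non-centrality is about r/√(1 − r²) × √50 = 0.2294 × 7.071 = 1.62. The critical t on 48 df is about 2.01. The miss probability is about Φ(2.01 − 1.62) = Φ(0.39) = 0.65, which agrees with the simulation below.

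**3. Type I error of the CFIR test.** Simulation with 10,000 runs per row, a true CFIR effect of zero, 7 candidates and a p < .05 screen. All confounding runs in the same direction. Each pair of values is for n = 50 / n = 49.

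| Confounders (correlation of each with CFIR) | r with outcome | Each missed | Screened set | All 7 fixed in advance |
|---|---|---|---|---|
| One (0.3) | 0.224 | 65% | 5.6% / 5.0% | 5.3% / 4.7% |
| One (0.5) | 0.224 | 65% | 5.9% / 5.6% | 5.2% / 5.0% |
| Two (0.5) | 0.158 | 80–81% | 7.5% / 8.0% | 4.6% / 4.9% |
| Three (0.4) | 0.129 | 86% | 8.7% / 9.0% | 5.0% / 5.1% |
| Seven (0.2) | 0.085 | 91% | 7.8% / 7.5% | 5.4% / 4.6% |
| Seven (0.3) | 0.085 | 91% | 11.4% / 11.2% | 5.0% / 5.2% |
| None: 7 related to CFIR only (0.3) | 0 | – | 3.5% / 3.2% | 5.2% / 4.7% |
| None: 3 related to outcome only | 0.3 | – | 5.3% / 5.1% | 5.1% / 5.1% |

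All rows with confounders use the plan's 5% covariate R-squared. With four confounders among seven candidates (r = √(0.05/4) = 0.112), each is missed in about 88% of runs. Type I error is then 6.3% to 10.9%, against about 5% for the fixed set.

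**4. What removes the inflation.**

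- Direction: with one of the four confounders biasing the opposite way, type I error falls to about 4% to 5%. With two reversed it was 2.9% to 4.9%.
- Threshold: in the four-confounder setting at 5% covariate R-squared, a p < .20 screen gives at most 5.3%. With two stronger confounders (r = 0.3 with the outcome, 0.5 with CFIR; 6 candidates) it is 9% to 10.5% at p < .05, 6.5% at p < .10 and 4.9% at p < .20.
- Number: settings with a single confounder, including stronger ones than in the table, gave 5.0% to 6.5%.

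**The case against.** The strongest reply is that the article does not say what the concern needs it to say. It does not call the association observed and mentions no test or threshold. The sentence could mean characteristics already known to predict delivery. A candidate list and selection criterion are commonly left to a fuller document, which is not shown here. This stands in part: data-driven selection is the natural reading, but it is an inference, and the p < .05 screen is assumed. The rule itself is not an omission, however. The article states it, and it turns on the outcome alone.

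Second, a reader might infer that the rule inflates the type I error as such, even to 13% or 21%. The document does not support that. Inflation needs several characteristics related to both CFIR and outcome, biases in the same direction and a strict screen. Program type, level of care and payment source have no obvious common direction. Figures of 13.2% and 20.9% arise only with a covariate R-squared of 15%, three times the plan's.

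Third, the stakes are modest. Aim 3 is a pooled, non-randomised analysis on scales that the article calls exploratory. The article itself grants that pooled analyses are inferentially limited, and no conclusion on NIATx effectiveness rests on this model. This is fair. Even so, H3 is a stated hypothesis with a two-tailed 5% test and a power claim.

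Fourth, different covariates for two outcomes are not an error in themselves. That is true, but the two CFIR coefficients are then harder to read together as evidence on one hypothesis.

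**Conclusion.** The concern holds in a conditional form. The firm part is omission: at about 50 programs, an outcome screen at p < .05 misses a confounder carrying the plan's whole 5% in about 65% of trials, and each of two to seven sharing it in about 80% to 91%. The stated purpose of controlling for other predictors would often not be met.

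The type I error part is a possibility, not a certainty: about 6% to 11% with several confounders biasing in the same direction, and near 5% with one confounder, opposing biases or a loose screen. The threshold, the correlations, the independence of the candidates and their number are all assumptions. What does not depend on them is the comparison: the fixed set stayed at 4.2% to 5.7% in these scenarios at n = 49 and 50, while the screened test depends on choices the article leaves open.

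The stated power is not in dispute. It would be too strong to say that fixing the covariates costs nothing, because that depends on how many degrees of freedom they use.

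**What to change.** Replace the entry rule with a covariate set named in advance on subject-matter grounds: program size, program type, ASAM level of care and payment source (all in Table 2), plus cohort. Use the same set for both dependent variables, whatever their observed association with the outcome. If the sentence was meant to refer to predictors known beforehand, naming them settles the matter.

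Keep the set to about 7 degrees of freedom. Size (as one continuous term) and cohort take 2, which leaves about 5 for the three categorical characteristics, so some categories will need collapsing, also in advance.

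The change is to wording and needs no new data. It costs degrees of freedom: at about 7 the stated 79% and 82% still apply for 50 programs (under the convention that reproduces them), and at 12 they fall to about 74% and 77%. Fixed adjustment deals only with the characteristics measured. It does not make the CFIR comparison a randomised one.

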##### Cost analysis

The economic cost analysis consists of two components. First, we will measure costs required to support participation in the implementation strategies (active and wait-list). In the second component, the cost analysis will examine potential changes in program finances (revenue and expenses) associated with delivering more integrated services. In contrast to the economic costs of integrating services, which includes costs not faced directly by the program are not part of any program’s operating budget, and thus savings to outside entities do not make interventions more feasible unless these savings are shared by the program. The cleanest and most comprehensive measure of the costs to a program providing integrated treatment is the pre-post (NIATx) change in total costs netting out any increased revenue, or adding in any loss in revenue, for the program. We will duplicate our successful earlier collection of costs, revenue, and admission information from each program [75]. For both study arms, we will collect archival cost information for two years before the intervention (pre-randomization) and two years from the start of the intervention implementation (post-randomization). Thus, the additional costs of NIATx will be the difference between the pre-post program change in costs and the pre-post control program change in costs. Change in costs will be calculated as:

Pre-post change in costs = (Total Costs)_post_ – (Total Costs)_pre_ - (Total Revenue)_post_ –(Total Revenue)_pre_.

The impact of improved integrated services could lead to additional (reflected as decreased costs) or lost (reflected as additional costs) revenues. By dividing each component by the number of admissions in that period, the net cost per admission can be derived. The economic analysis will identify important sustainability implications and could influence future stakeholder implementation decisions [76].

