## Methods/study design

### Overview

The project represents a collaboration between Stanford University, University of Wisconsin-Madison, and the Division of Behavioral Health and Recovery (DBHR) located in the Washington State Department of Social and Health Services. The study uses a cluster randomized wait-list control group design. Fifty community-based addiction treatment programs located in the State of Washington will be assigned to one of two cohorts (Fig. 2) during an index 12-month period: 1) NIATx implementation strategies (Cohort 1), or 2) wait-list control (Cohort 2).

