**Fig. 2 Fig2:**
[figure not shown]
NIATx Implementation Strategy Study Design. The community programs are randomized to NIATx (Cohort 1) or Wait List (Cohort 2) with four data collection time points

The programs will use the NIATx implementation strategy to implement changes targeting integrated treatment services. The study will assess the effectiveness of the NIATx implementation strategies to improve integrated services for persons with co-occurring substance use and mental health disorders. Hypothesized effects are that relative to the wait-list, NIATx strategies will improve implementation (penetration and fidelity) and patient care outcomes (Aim 1 and Aim 2). Variation in the extent of and fidelity to the NIATx implementation strategies will be examined across the entire sample (Aim 3). The specific aims and hypothesis are detailed in Table 1. Figure 3 shows the overall study timeline. Recruitment began in April 2016 and the active intervention period for Cohort 2 ends in June 2018.

**Table 1 Tab1:** Study Specific Aims and Hypotheses

Aim	Hypotheses
Specific Aim 1: Relative to wait-list, to determine if NIATx strategies improve *implementation fidelity outcomes*.	H1: *NIATx strategies will produce increased integrated service fidelity at the program level*.
Specific Aim 2: Relative to wait-list, to determine if NIATx strategies improve *implementation penetration outcomes*.	H2: *NIATx strategies will produce increased penetration rates in integrated services, evidenced by proportion of program patients screened, diagnosed and receiving integrated medication and psychosocial services.*
Specific Aim 3: Across entire sample, to evaluate variation in the *extent of and fidelity to NIATx* strategies.	H3: *Programs with more facilitating factors, articulated by the Consolidated Framework for Implementation Research (CFIR) Index dimensions will be more likely to complete the requisite tasks of the NIATx protocol and do so with greater fidelity.*

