### NIATx implementation strategy

Programs in the NIATx intervention will be assigned a NIATx trained process improvement coach who leads the active implementation phase. Over a 12-month active implementation period, the coach works with executive directors, change leaders and teams. Coaching includes a one-day site visit and individual monthly phone conferences (10 h total) with each program.

Prior to the site visit, the coach will introduce the project, review initial DDCAT results, discuss how to conduct a walk-through [64] and set the stage for the site visit. The site visit will use a standardized agenda to ensure fidelity. During the visit, the coach will meet with executive leadership, review the walk-through and DDCAT assessment results, and train staff on the use of the NIATx implementation strategies. With their coach, the program will utilize results from the DDCAT assessment to identify areas for improvement, implement change projects and assess their impact.

After the site visit, the coach will conduct bi-monthly coaching calls with their assigned programs for the 1st quarter of the implementation period and monthly calls thereafter. In the individual calls, the coach and change team will review change projects, discuss successes, and identify new change projects. In addition to individual coaching calls, the coach provides support through learning sessions and group coaching calls.

Two group calls, moderated by the coach, will involve change leaders from multiple programs and provide an opportunity for peer-to-peer sharing. On these calls, the change leaders will discuss common change-related issues, progress, and exchange innovative implementation strategies with their peers. The calls will also allow the coach to share new strategies and discuss implementation issues such as sustainment of organizational change.

The study will include two one-day coach-led learning sessions for all programs within a cohort. Learning sessions promote peer-to-peer sharing about specific goals and objectives using a tailored agenda. The first learning session will teach programs how to use NIATx process improvement strategies through skill development activities such as how to identify change opportunities, develop PDSA cycles and effective use of data to drive change. The second learning session will include program presentations about change efforts and discuss how to develop sustainment plans to continue to improve integrated services.

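### The two-year post window for the net-cost contrast runs past the 12-month randomized period, so most or all of the wait-list arm's own NIATx year counts as control experience

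*Protocol article*

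**What the plan says.** The Cost analysis section has two components. The first is a direct measurement: "First, we will measure costs required to support participation in the implementation strategies (active and wait-list"). The second looks at changes in program finances, net of revenue, and sets one data window. Its earlier half reads "For both study arms, we will collect archival cost information for two years before the intervention (pre-randomization"). The later half, which likewise applies to Cohort 1 and Cohort 2 alike, covers "two years from the start of the intervention implementation (post-randomization"). The next sentence draws the estimand from that window: "the additional costs of NIATx will be the difference between the pre-post program change in costs and the pre-post control program change in costs". No shorter analysis window is given, and nothing is said about the wait-list arm taking up NIATx later.

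The design sections set the exposure periods:

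- Overview: programs are assigned "during an index 12-month period: 1) NIATx implementation strategies (Cohort 1), or 2) wait-list control (Cohort 2").
- NIATx implementation strategy (Methods): "Over a 12-month active implementation period, the coach works with executive directors, change leaders and teams".
- Overview, text following Fig. 2: "Recruitment began in April 2016 and the active intervention period for Cohort 2 ends in June 2018".

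**The concern.** A difference in differences attributes a cost to NIATx only while one arm is exposed and the other is not. Under this design that holds for the 12-month index period. The cost window is twice as long, so the comparison arm's post-period contains programs that are themselves in active implementation. Their implementation-year costs are then subtracted from those of Cohort 1.

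The section calls the pre-post net change the cleanest and most comprehensive measure of cost to a program, and says that the economic results could influence stakeholders' later implementation decisions. A figure labelled as the additional cost of NIATx that leaves out much of the active-year cost could mislead those readers. It also sits badly with the opening of Data and power analysis, which confines the presentation to the experimental comparison because pooled-group analyses are inferentially limited.

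**Working it through.** The protocol states no cost amount, so there is no figure to reproduce. Two checks apply.

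**1. Calendar overlap.** Inputs: recruitment from April 2016, Cohort 2 active period ending June 2018, active period of 12 months, post window of 24 months. Taking the end as the close of June, Cohort 2's active period is July 2017 to June 2018. Cohort 1 cannot have started before April 2016. If the wait was at least 12 months, it started no later than July 2016.

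| Cohort 1 start | 24-month window ends | Cohort 2 active months inside it |
|---|---|---|
| April 2016 | March 2018 | 9 |
| May 2016 | April 2018 | 10 |
| June 2016 | May 2018 | 11 |
| July 2016 | June 2018 | 12 |

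**2. Algebra of the stated contrast.** Let C be the net cost of Cohort 1's active year and S its net cost in the following year. Let f be the share of Cohort 2's active year inside the window (9/12 = 0.75 to 1) and q the wait-list arm's active-year net cost relative to C. Assume that costs are spread evenly over the active year and that the waiting period adds nothing. Background trends common to both arms cancel.

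- Cohort 1 change: C + S
- Cohort 2 change: q × f × C
- Stated contrast: (C + S) − qfC = S + (1 − qf)C

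With q = 1 and f = 1 this is S. With q = 1 and f = 0.75 it is S + 0.25C. As a share of the two-year cost C + S:

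| S/C (assumed) | f = 1 | f = 0.75 |
|---|---|---|
| 0 | 0% | 25% |
| 0.25 | 20% | 40% |
| 0.5 | 33% | 50% |
| 1 | 50% | 62.5% |

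Unequal arm costs: with f = 1, q = 0.8 gives S + 0.2C and q = 1.2 gives S − 0.2C. With f = 0.75 the same values of q give S + 0.4C and S + 0.1C. Over these ranges the amount subtracted, qf, runs from 0.6 to 1.2 times C.

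**Direction.** The section expects that integrated services may raise or lower revenue, so S can be negative. Illustrations with C = 100, q = 1, f = 1:

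- S = −20: two-year cost 80, stated contrast −20 (sign reversed).
- S = −60: two-year cost 40, stated contrast −60 (sign reversed).
- S = −150: two-year cost −50, stated contrast −150 (further from zero).

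**After restriction to the index period.** Cohort 1 change = C and Cohort 2 change = 0, so the contrast is C.

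**The case against.** The best defence has four parts.

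- *Participation costs are measured elsewhere.* This stands. The first component measures them directly in both arms, and the operational survey described under Data collection/variables asks about staff time and cost spent on NIATx. A reader might infer that the trial would end up reporting NIATx as nearly free to programs. The documents do not support that, since only the net-finance contrast is affected. The direct measurement does not, however, repair that contrast.
- *Two years is a data-collection window, and a fuller plan may handle years separately.* This stands in part. The two-year phrase is attached to collection, but the following sentence derives the estimand from it and no other window is stated. Pooling both years is the natural reading.
- *Exact cancellation and bias toward zero are not established.* This stands. Exact cancellation needs full overlap and equal active-year costs in the two arms, and the protocol states neither. Attenuation toward zero is assured only if C and S share a sign, which cannot be assumed for a measure net of revenue.
- *Financial effects may accrue after the active year, so a 12-month cut answers a narrower question.* This is true, but the wait-list design gives no clean randomized comparison in year 2 with or without the cut.

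A reader might also align each arm to its own NIATx start, which would make the contrast (C + S) − (C + S) = 0 under equal costs. The text does not favour that reading: it ties the windows to before and after randomization in both arms, which points to one common anchor.

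**Conclusion.** The concern holds for the program-finance contrast. As written, it compares two years that include NIATx implementation in Cohort 1 with two years that include 9 to 12 months of active NIATx in Cohort 2. It therefore estimates roughly S, or S + 0.25C at the shortest overlap with equal arm costs, and neither C nor C + S. Most or all of the active-year net cost is removed, and the error can go either way or change the sign.

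This rests on a common post-randomization anchor, additive yearly costs, and a lag of about 12 months inferred from the text because Figs. 2 and 3 are not shown. The values of S/C and q are assumptions shown as ranges.

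The cost analysis is not among the three aims in Table 1, carries no hypothesis and is not a primary outcome. Aims 1 to 3 are unaffected. It should be fixed, as a defect in a secondary analysis.

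**What to change.** State that the randomized net-cost contrast uses the 12-month index period only, set against the 12 months before randomization or the annualized two-year pre-period, so that both sides cover the same length of time. Report year 2 separately and label it non-randomized: Cohort 1's sustainment year descriptively, and Cohort 2's active year as a within-program pre-post change. Keep the direct participation-cost component as planned.

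The change is wording plus a date cut on data the plan already collects, provided that the archival records can be split by year. The price is one post-year instead of two in the randomized contrast, with no randomized comparison for financial effects that accrue later.

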### Data and power analysis

The analyses will include a quantitative assessment of Aims 1 to 3 and an economic cost analysis. Table 1 outlines the study aims and hypotheses. The data and power analysis approaches are presented in sequence for each aim by hypothesis for the experimental comparison only, as the pooled-group analyses have inferential limitations. Power was assessed using SamplePower 3.0 [73].

#### Specific aim 1

For hypothesis 1, the program is the unit of analysis, and DDCAT (fidelity) scores represent the dependent variable and the cohort assignment (NIATx vs. wait-list) is the independent variable. A two tailed analysis of covariance (α = 0.05) with 25 programs per cohort group will compare post- implementation mean fidelity scores between groups, with pre-implementation scores as the covariate. With a correlation between pre- and post- implementation DDCAT scores equal to 0.5, this analysis has power (β = .86) to detect a large effect. Prior research concerning one-year changes in DDCAT scores suggests that we can expect a large effect [62].

#### Specific aim 2

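### The cost-change formula subtracts pre-period revenue where the text requires it to be added back, an error of twice pre-period revenue for each program

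*Protocol article*

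**What the plan says.** The Cost analysis section of the protocol article has two components: the cost of supporting participation in the implementation strategies, and the change in program finances. The formula belongs to the second.

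- The measure is first defined in words, as the pre-post "change in total costs netting out any increased revenue, or adding in any loss in revenue, for the program".
- The calculation rule, introduced by "Change in costs will be calculated as", is then displayed: "Pre-post change in costs = (Total Costs)_post_ – (Total Costs)_pre_ - (Total Revenue)_post_ –(Total Revenue)_pre".
- The sentence after the formula gives the direction of the revenue effect: better integrated services "could lead to additional (reflected as decreased costs) or lost (reflected as additional costs) revenues".
- The result is used in two ways. For the arm comparison, "the additional costs of NIATx will be the difference between the pre-post program change in costs and the pre-post control program change in costs". For a unit cost, "By dividing each component by the number of admissions in that period, the net cost per admission can be derived".

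The cost data cover two years before and two years from the start of the intervention, in both arms.

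**The concern.** The prose and the formula describe different quantities. The prose nets the change in revenue against the change in costs. The displayed line has a minus sign before both revenue terms and no bracket around the revenue pair, so it deducts post-period and pre-period revenue together.

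This is the only formula displayed in the cost analysis, it is worded as the operative rule, and an analyst could code it literally. If that happened:

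- A program's result would be positive only if its cost increase exceeded the sum of both periods' revenue, so practically every program would appear to save money.
- The per-admission figure would inherit the error.
- The arm contrast would absorb any imbalance in baseline revenue, which has nothing to do with NIATx.

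The section presents the economic results as relevant to sustainability and to later implementation decisions, so a wrong sign here would mislead the readers for whom the analysis is meant.

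**Working it through.** **Inputs.** The printed formula, the prose definition, the direction of the revenue effect, and the two uses of the measure all come from the Cost analysis section. The 25 programs per arm come from Data and power analysis, Specific aim 1. The article gives no cost or revenue figures, so there is no stated result to reproduce; all money amounts below are illustrative.

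Write C for total costs, R for total revenue and A for admissions.

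**Step 1: the two definitions.**

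- Printed: P = C_post − C_pre − R_post − R_pre
- Prose: D = (C_post − C_pre) − (R_post − R_pre) = C_post − C_pre − R_post + R_pre
- Difference: P − D = −2 × R_pre

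The difference depends only on pre-period revenue. It does not shrink if the intervention has no effect.

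**Step 2: single programs.** C_pre = R_pre = 1000 in every row.

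| Scenario | C_post | R_post | Printed P | Prose D | P − D |
|---|---|---|---|---|---|
| Nothing changes | 1000 | 1000 | −2000 | 0 | −2000 |
| Costs +50, revenue +20 | 1050 | 1020 | −1970 | +30 | −2000 |
| Costs +100, revenue +150 | 1100 | 1150 | −2050 | −50 | −2000 |
| Costs +100, revenue −50 | 1100 | 950 | −1850 | +150 | −2000 |

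In the second and fourth rows the sign of the result reverses: a net loss is reported as a large saving. If R_pre is the total for the two-year pre-period, the error of 2 × R_pre equals about four years of a program's revenue (2 × 2 years).

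**Step 3: per admission.** Dividing each component by the admissions of its own period leaves an error of −2 × R_pre / A_pre.

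**Step 4: the arm contrast.** The error in NIATx minus control is −2 × (mean R_pre in NIATx − mean R_pre in control). For illustration, NIATx programs have costs +100 and revenue +150, control programs have costs +20 and revenue +20, and pre-period costs equal pre-period revenue within each arm. The correct contrast is (100 − 150) − (20 − 20) = −50 throughout.

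| Mean R_pre, NIATx | Mean R_pre, control | Contrast as printed | Correct contrast | Error |
|---|---|---|---|---|
| 1000 | 1000 | −50 | −50 | 0 |
| 1000 | 900 | −250 | −50 | −200 |
| 1000 | 1100 | +150 | −50 | +200 |

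**Step 5: size of the chance error in the contrast.** With 25 programs per arm and a between-program coefficient of variation CV for R_pre, the standard deviation of the error, relative to mean R_pre, is 2 × CV × √(2/25).

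- √(2/25) = 0.283
- CV = 0.5: 2 × 0.5 × 0.283 = 0.28
- CV = 1.0: 2 × 1.0 × 0.283 = 0.57

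In the illustrative units, a mean of 1000 and a standard deviation of 500 give 2 × 500 × 0.283 = 283, against a true contrast of −50. The CV range is an assumption; the article offers nothing from which to estimate it.

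**The case against.** The strongest reply is that this is a notational slip and not a wrongly specified analysis. The prose fixes the intended measure correctly both before and after the formula. The typography also points to lost grouping: a long dash joins each post/pre pair, while a plain hyphen separates the cost pair from the revenue pair. A literal calculation would give an unchanged program a saving of twice its baseline revenue, which an analyst would probably notice. The article reports no cost result and shows no code, so no wrong figure is known to exist.

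Most of this stands as an account of how the error arose and how serious it is. Missing brackets are the likely cause. It does not make the printed rule right, because that rule still contradicts its own definition. Brackets lost when the text was read from the PDF cannot be ruled out, but nothing shows it: the parentheses around all four terms survived.

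Three further points also stand. The primary outcomes are fidelity and penetration, none of the three aims in Table 1 concerns cost, and the cost analysis has no hypothesis or power statement. The first cost component does not use this formula. In the arm contrast the error cancels in expectation under randomization, so what remains there is added variance and chance imbalance, not systematic bias. All of these limit the severity without removing the error.

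**Conclusion.** The concern holds. As printed, the formula contradicts the prose around it and, if applied literally, understates each program's net cost change by exactly twice its pre-period revenue. That part is algebra and needs no assumption.

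The effect on the arm contrast is zero on average but not in a single realized trial. The figure of about 28–57% of mean pre-period revenue for its standard deviation rests on 25 programs per arm and the assumed CV of 50–100%.

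The correction is needed before the cost analysis is run or reported, because literal use would make the program-level and per-admission results meaningless. It ranks below a defect in a primary analysis: Aims 1–3 are untouched, and the intended measure can be recovered from the text.

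**What to change.** Replace the displayed line with:

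Net change in costs = [(Total Costs)_post − (Total Costs)_pre] − [(Total Revenue)_post − (Total Revenue)_pre]

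Writing the per-admission version out in full would prevent the same slip there. It only makes explicit the division that the section already intends:

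[C_post / A_post − C_pre / A_pre] − [R_post / A_post − R_pre / A_pre]

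Then check that the analysis code uses the bracketed form. A simple test is a program with identical costs, revenue and admissions in both periods, which must return 0. The cost is one line of text and a check of one line of code; no new data and no change to the design are required.
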